### Adverse events

Research nurses will report any subjects that they are concerned about to their local academic GP associated with the project. The GP will decide upon a course of action, up to and including reporting the matter to the subject's own GP (with subject permission). Nurses will cease interviewing subjects who report feeling tired or uncomfortable during the interview. The subject will be given the option of completing the interview at a later time, using only the data collected to that point, or withdrawing from the study.

### Sample size

It was calculated that 45 patients with dementia in each group (Waitlist and Intervention) would give a power of 0.9 to detect a 7% difference between the change in pre and post scores on any of the four domain scales of the WHOQOL-BREF with a type 1 error of .05. The population standard deviation used is 18.5 [32] and the Pearson correlation coefficient between the pre and post scores for both groups is assumed to be 0.7, based on pilot data available from the University of Melbourne.

The hierarchical nature of the study design will probably lead to some within cluster correlations and the greatest impact of this is likely to be associated with patients clustered within a GP practice. Clustering within each GP may be discounted, as it is anticipated that most GPs will have less than five patients with dementia in this study. Assuming an intra-class correlation coefficient of 0.05 and an average cluster size of 5 patients with dementia in a practice, this gives a design effect of 1.45 and a total sample size of 54 patients per group. We will therefore allow for 56 patients with dementia in the waitlist group and 112 in the intervention group to allow for comparison of outcomes between the waitlist and intervention groups overall. This sample size also allows comparison of "case finding" and "screening" patients and their support persons within the group. It is assumed that about 50% of participants will be screening and 50% case finding. Thus, we aim to recruit 168 participants with dementia overall. Based on a dementia prevalence of approximately 10% in over 75 year old Australians [37], we aim to recruit a total of 2,000 participants.

For the GDS, following the same set of assumptions and approach as for the WHO QOL-BREF (power, type 1 error and correlations), 45 patients in both the Intervention and Waitlist groups would allow detection of an average difference in the change in pre and post scores of 0.9 points on the 15 point GDS, using a standard deviation of 2.39 [28]. The cluster effect would be the same as for the WHOQOL-BREF.

For an estimate of test re-test reliability on the GPCOG a sample size of 100 will be used to ensure the correlation is estimated to a reasonable precision. The 95% confidence interval for a Pearson correlation of 0.9 would be [0.86, 0.93] and for a correlation of 0.80 [0.73, 0.85].

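### The sample size of 45 per group does not give 90% power for the two-group comparison of change: the stated inputs need 89 per group, and the planned 56/112 gives about 78% (WHOQOL-BREF) and 77% (GDS) at design effect 1.20

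*Protocol article*

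**What the plan says.** The Sample size section of the protocol article sets the target for the first primary patient outcome: "45 patients with dementia in each group (Waitlist and Intervention) would give a power of 0.9 to detect a 7% difference". The quantity compared is a "7% difference between the change in pre and post scores on any of the four domain scales of the WHOQOL-BREF". Alpha is set at 0.05, without saying whether one-sided or two-sided. Two further inputs follow. On spread, the section says: "The population standard deviation used is 18.5". On how closely the two measurements of a patient agree, it says that "the Pearson correlation coefficient between the pre and post scores for both groups is assumed to be 0.7".

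For the second primary patient outcome, the GDS, the same section keeps the power, type 1 error and correlation, takes an SD of 2.39, and says that "45 patients in both the Intervention and Waitlist groups would allow detection of an average difference" in change of 0.9 points.

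For clustering it continues: "Assuming an intra-class correlation coefficient of 0.05 and an average cluster size of 5 patients with dementia in a practice". It prints a design effect of 1.45, arrives at 54 per group, and settles on 56 waitlist and 112 intervention patients with dementia. Statistical analyses places the comparison of patient outcomes between Intervention and Waitlist at twelve months. Study drop outs/withdrawals expects 180 patients with dementia at that time and 162 at 24 months.

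**The concern.** The comparison is between two independent groups, so the variance of the estimated effect is the sum of two arm variances, and the required number per group carries a factor 2. The printed 45 is about half of what that formula gives, and it is so for both primary patient outcomes even though their SDs and target differences are unrelated. The later steps (54, then 56/112) build on 45, so any shortfall carries through.

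At stake is how a null result would be read. With the stated 90% power, a trial that finds nothing would be taken as fairly strong evidence against a 7-point or 0.9-point effect. If true power is nearer 78%, the chance of missing such an effect is about twice the 10% that the section implies.

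**Working it through.** **Inputs, all from Sample size unless noted.** WHOQOL-BREF: difference 7, SD 18.5. GDS: difference 0.9, SD 2.39. Correlation 0.7, alpha 0.05, power 0.90. ICC 0.05, 5 patients per practice. Final numbers 56/112. From Study drop outs/withdrawals: 180 patients at 12 months, split here 2:1 as 60/120.

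**Assumptions.** The 7% is read as 7 points on a 0-100 domain scale. Testing is two-sided, because the section does not state sidedness. The normal approximation is used: (1.96 + 1.2816)² = 10.507.

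**SD of change** = SD × √(2(1 − r)).
- WHOQOL-BREF: 18.5 × √0.6 = 14.33
- GDS: 2.39 × √0.6 = 1.851

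**Reproducing the printed 45.** Without the factor 2, n = 10.507 × (SD of change / difference)².
- WHOQOL-BREF: 10.507 × 14.33² / 7² = 44.03, rounded up to 45
- GDS: 10.507 × 1.851² / 0.9² = 44.46, rounded up to 45

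**Two-group requirement.** n per group = 2 × the above.
- WHOQOL-BREF: 88.07, so 89
- GDS: 88.92, so 89

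**Design effect.** 1 + (5 − 1) × 0.05 = 1.20, and 45 × 1.20 = 54, the section's own inflated figure. The printed 1.45 would give 45 × 1.45 = 65.25. So 1.20 is the value consistent with both the inputs and the 54. Results with 1.45 are shown as well.

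**Power** = Φ(difference / SE − 1.96), with SE = SD of change × √(DE × (1/n₁ + 1/n₂)).

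Example, WHOQOL-BREF at 56/112 with DE 1.20: SE = 14.33 × √(1.2 × (1/56 + 1/112)) = 2.569; 7 / 2.569 = 2.725; Φ(0.765) = 77.8%.

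| Patients (waitlist/intervention) | Design effect | WHOQOL-BREF, 7 points | GDS, 0.9 points |
|---|---|---|---|
| 45/45 | none | 63.9% | 63.5% |
| 56/112 | none | 84.7% | 84.4% |
| 56/112 | 1.20 | 77.8% | 77.4% |
| 56/112 | 1.45 | 69.8% | 69.4% |
| 60/120 (12 months) | 1.20 | 80.5% | 80.2% |

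**Difference detectable with 90% power at 56/112, DE 1.20** = 3.2416 × SE.
- WHOQOL-BREF: 3.2416 × 2.569 = 8.3 points
- GDS: SE = 1.851 × √(1.2 × (1/56 + 1/112)) = 0.332; 3.2416 × 0.332 = 1.08 points

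**Sensitivity, WHOQOL-BREF at 56/112 with DE 1.20.**
- One-sided test on change scores: 86%.
- Two-sided test adjusted for baseline: the residual SD is 18.5 × √(1 − 0.7²) = 13.21, so SE = 2.369, power is 84.0% and the difference detectable with 90% power is 7.7 points.
- One-sided and baseline-adjusted together: 90.5%.

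**The case against.** The strongest reply has several parts.

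- **Origin of 45.** A reader might infer that a one-group paired formula was used. The article names no formula, so this stays an inference. Leaving out the 2 in 2(1 − r) within a two-group formula gives the same number, and a one-sample t calculation for WHOQOL-BREF would give 46 rather than 45. The finding does not depend on the origin: 45 per group falls short whatever produced it.
- **Other readings near 45.** They exist. A one-sided baseline-adjusted test at 2:1 needs 46 in the waitlist arm, and a one-sided baseline-adjusted test averaging two follow-ups needs 44 per group. The section describes equal groups of 45 and a pre-post change, and mentions neither one-sided testing nor baseline adjustment. A two-group change-score n of 45 would need a correlation of about 0.85, not 0.7.
- **Final numbers and time point.** The 2:1 allocation and the larger number expected at twelve months recover part of the loss, to about 80%. This stands, and it is why 78% should not be given as the single true figure.
- **Analysis model.** A reader might infer that an unadjusted change-score analysis is fixed. It is not: the change score appears only in the sample size reasoning, and Statistical analyses foresees mixed effects models. With baseline adjustment the shortfall is smaller (84%), but it remains.
- **Case finding versus screening.** A reader might carry the shortfall over to this contrast and quote a power for 56 against 56 with the same design effect. The article does not support that. Case-finding status is assigned patient by patient, so both types can occur within one practice and the between-practice design effect does not apply. The section says only that the size allows this comparison and claims no 90% power for it.

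**Conclusion.** The 90% power claim is wrong as written for both primary patient outcomes. On the section's own inputs the two-group comparison needs 89 patients per group before clustering, about twice the 45 stated. Two-sided change-score power at the planned 56/112 lies between about 70% (design effect 1.45) and 78% (1.20) for WHOQOL-BREF, and between 69% and 77% for the GDS. It is about 80% for both at the twelve-month numbers with 1.20.

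This rests on reading 7% as 7 points, on two-sided testing, on the stated SDs and correlation, and on a 2:1 split of the 180. The two-group requirement is arithmetic under those assumptions; only the explanation of how 45 arose is inferred. Once the stated clustering is allowed for, 90% at 56/112 is reached among the variants tried only with one-sided testing and baseline adjustment combined, and the article describes neither.

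**What to change.** Restate the sample size paragraph with the two-sample formula, naming the sidedness, the design effect and the time point. With two-sided 0.05, design effect 1.20 and 56/112, either of these statements is accurate:

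- about 78% power for 7 WHOQOL-BREF points and about 77% for 0.9 GDS points; or
- 90% power for about 8.3 WHOQOL-BREF points and about 1.08 GDS points.

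If the mixed model already foreseen under Statistical analyses will adjust for the baseline score, WHOQOL-BREF power may instead be given as about 84% for 7 points (90% for about 7.7 points), provided that the adjustment is stated and the same design effect is taken to apply. State also that the 7% means 7 points, if that is the intention. No power figure for case finding versus screening should be derived from this calculation.

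The cost is a rewritten paragraph and a less favourable stated power. No added recruitment is proposed, and the Abstract reports that 2,034 subjects had already been recruited.

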### Patients and support persons

Patients will be recruited by a mail out from each consenting GP to all eligible patients on their database. Patient participants will return their consent in reply paid envelopes to the study centre. Patients will be interviewed by study personnel blind to the group allocation of the patient and their GP. For patients scoring in the dementia range on the CAMCOG instrument (described below), the interviewer will request that they nominate a support person, if available, to take part in the study. Nominated support people will be given a consent form and information sheet for recruitment into the study.

Inclusion criteria for patients:

• Aged 75 years or over

• Listed on participating GPs' databases

• Visited recruited GPs within the last 24 months

• Consent to a home visit or surgery visit by project staff

• Speak and understand English

Inclusion criteria for support persons:

• Identified as a carer or support person by a patient scoring in dementia range on CAMCOG instrument

• Prior consent from the person with dementia for his/her carer to participate in the study

• Speak and understand English

• Consent to a home visit or surgery visit by the project staff.

Exclusion criteria for patients:

• Parkinson's disease, multiple sclerosis, motor neuron disease or central nervous system inflammation

• Psychotic symptoms prior to recruitment

• Developmental disability

• Insufficient English to complete a psychometric assessment (judged by interviewer)

• Progressive malignancy

• Substance abuse

• Deemed too sick to complete study by the GP

• Lives in a residential aged care facility at entry to the study

• Does not meet inclusion criteria

• Valid and informed consent cannot be obtained from the person involved and they do not have a person responsible for them.

Exclusion criteria for support persons:

• Insufficient English to complete testing (judged by the interviewer)

• Non-consenting patient-participant

• Does not consent to a home visit or surgery visit by the project staff.

• Too unwell to participate

• De not meet inclusion criteria.

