### Outcome measures

Primary outcome measures related to the first aim (collected at baseline, 12 months and 24 months) are:

1. World Health Organization Quality of Life-Bref Scale (WHOQOL-BREF) score for patients

2. Geriatric Depression Scale score for patients

Secondary outcome measures related to the first aim (collected at baseline, 12 months and 24 months) are:

1. World Health Organization Quality of Life-Bref Scale (WHOQOL BREF) for carers

2. Beck Depression Inventory score for carers

3. Agreement of GP audit for dementia with CAMCOG instrument

4. GP differential diagnosis for dementia

5. GP identification and treatment of reversible causes of dementia 6.GP dementia related referrals made

7. General Practice Assessment Questionnaire score

8. Acceptability of the process scale score

9. Services accessed

To meet the second aim of the study, screening and case finding groups (as defined above) will be compared on primary and secondary outcome measures 1 and 2 as listed above. The GPCOG score will be compared with the gold standard of the CAMCOG score to address the third aim of the study. The performance of the GPCOG against the CAMCOG will also be compared with that of the MMSE against the CAMCOG, as the MMSE is widely used to screen for dementia.

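### The patient sample size is said to serve the support-person comparison within the intervention arm too, with no allowance for patients who have no participating support person

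*Protocol article*

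**What the plan says.** The Sample size section starts from the statement that "45 patients with dementia in each group (Waitlist and Intervention) would give a power of 0.9". The target is a between-group difference in change of 7% on a WHOQOL-BREF domain, tested at alpha 0.05. For the inputs it gives an SD of 18.5 and a pre-post correlation of 0.7. After an allowance for clustering it arrives at 54 patients per group and plans 56 in the waitlist arm and 112 in the intervention arm. Half of the participants are assumed to be screening and half case finding. It then concludes: "This sample size also allows comparison of 'case finding' and 'screening' patients and their support persons within the group". The Statistical analyses section places this comparison inside the intervention arm.

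Under Patients and support persons, a support person enters through a patient who scores in the dementia range: "the interviewer will request that they nominate a support person, if available, to take part in the study". A further condition is "Prior consent from the person with dementia for his/her carer to participate in the study". The support person must also consent to a visit, have adequate English and be well enough. The ADL description likewise provides for patients with no support person available, because the patient then completes the form.

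Outcome measures lists carer WHOQOL-BREF and "Beck Depression Inventory score for carers" as the first two secondary outcomes and includes both in the case-finding versus screening comparison.

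**The concern.** Every count in the calculation is a count of patients. The entry rules give at most about one support person per patient, and fewer wherever nobody is available, the patient declines, or the carer declines or is ineligible. The plan carries the patient figure over to carers unchanged, and 56 exceeds 54 by only two people.

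The outcomes on which carers are compared are not covered either. The section sizes WHOQOL-BREF and GDS for patients. Using the same WHOQOL-BREF inputs for carers is an unstated assumption, and the Beck Depression Inventory has neither a standard deviation nor a target difference.

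What is at stake is how a null carer result will be read. Better outcomes for carers are part of the second aim, and a reader would rely on the statement that the comparison was adequately sized.

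**Working it through.** **Inputs.** From Sample size: difference 7 points, SD 18.5, correlation 0.7, alpha 0.05 (taken as two-sided), power 0.90, ICC 0.05, cluster size 5, arms of 56 and 112, a 50:50 split. From Study drop outs/withdrawals: 180 patients with dementia at 12 months and 162 at 24 months. Take-up by support persons is not given; 60–80% is assumed for illustration.

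**Step 1: the plan's 54.**
- SD of change = 18.5 × √(2 × (1 − 0.7)) = 14.33.
- (1.96 + 1.2816)² × 14.33² / 7² = 44.03, which rounds up to 45. This is the one-sample form.
- Design effect = 1 + (5 − 1) × 0.05 = 1.20, and 45 × 1.20 = 54. The printed 1.45 would give 65.25, so 54 rests on 1.20, which is used below.

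**Step 2: patients per subgroup, and the take-up needed for 54 carers.** At 2:1 allocation and a 50:50 split, each subgroup is one third of all patients with dementia.

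| Basis | Patients with dementia | Per subgroup | Take-up needed (54 ÷ per subgroup) |
|---|---|---|---|
| Planned size | 168 | 56 | 96.4% |
| 12 months | 180 | 60 | 90% |
| 24 months, before incident cases | 162 | 54 | 100% |

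**Step 3: carers and power at assumed take-up.** Power by the plan's own formula = Φ(7 × √(n/1.20) / 14.33 − 1.96). Full take-up of 56 gives 0.92, and n = 54 gives 0.91.

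| Take-up | Carers from 56 | Power | Carers from 60 | Power |
|---|---|---|---|---|
| 80% | 44.8 | 0.85 | 48 | 0.87 |
| 70% | 39.2 | 0.80 | 42 | 0.82 |
| 60% | 33.6 | 0.73 | 36 | 0.76 |

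**Step 4: fewer carers per practice.** If the cluster size shrinks with take-up f, the design effect is 1 + (5f − 1) × 0.05. Then 56f ÷ (0.95 + 0.25f) ≥ 45 gives f ≥ 42.75/44.75 = 95.5%. From 60 patients, f ≥ 42.75/48.75 = 87.7%. From 56 patients, power at 80% and 60% take-up becomes 0.86 and 0.77. The picture hardly changes.

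**Step 5: intervention versus waitlist carers.** A 56:112 comparison carries the information of 2 × 56 × 112 / 168 = 74.7 per group. It drops below the equivalent of 54 only when take-up is under 54/74.7 = 72%. With the 12-month numbers, 2 × 60 × 120 / 180 = 80, and the limit is 54/80 = 67.5%.

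**The case against.** The strongest reply is that no shortfall has been demonstrated. The article gives no take-up rate, fewer carers than patients need not mean fewer than 54, and 54 was derived for patient outcomes. All of that stands. A reader might infer that the carer comparisons certainly miss the required size, but the documents support only a conditional statement.

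Three other inferences go too far:

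- **The between-arm carer comparison has the same problem.** It does not. The larger intervention arm gives it slack down to about 72% take-up (step 5).
- **Power is nearer one half.** As a two-group comparison of change with clustering at 1.20, power at 60–80% take-up is about 0.45–0.56. But even full take-up of 56 gives only 0.66 on that basis. Most of the loss therefore comes from the one-sample formula, a separate error in the same section that affects patients as well.
- **Screening patients are the least likely to have a carer.** This is plausible, but nothing in the article links nomination to memory complaints.

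It can also be said that Outcome measures ranks the carer scales as secondary, that the sentence names no power for carers, and that a condensed article may leave inputs for a secondary scale to the full protocol. The ranking limits the importance, although the Abstract names carer outcomes as primary. The lack of BDI inputs would be no finding by itself. It counts here because the article draws a positive conclusion that the size is sufficient.

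**Conclusion.** The point holds in a limited form. The statement that the sample size also serves support persons has no support in the article, and by the plan's own numbers it is true only if nearly every patient supplies a participating carer: at least about 96% of 56, 90% of 60 at 12 months, or all of 54 at 24 months before the small number of incident cases.

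The article fixes 12 months for the between-arm health outcomes but names no time point for the subgroup comparison, so all three bases are shown. The 12-month basis is the more lenient of the two follow-up times.

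The cost of 60–80% take-up is moderate: power of 0.73–0.87 across the two bases in step 3, against 0.90. These figures assume that the patient SD and correlation apply to carers, and that the plan's formula and the 1.20 design effect are accepted for the sake of comparison. For the BDI no power can be computed at all.

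**What to change.** In the Sample size section:

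1. Remove support persons from the sentence on adequacy.
2. State the expected number of support persons per subgroup as patients with dementia times an assumed take-up, over a range. From 56 patients, 60–80% gives about 34–45; from 60 patients, 36–48.
3. Give the difference in carer WHOQOL-BREF detectable at those numbers, once the two-group formula and the design effect in the same section have been settled.
4. State that the carer comparisons, including the BDI, are not powered and will be reported as estimates with confidence intervals.

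This takes one or two sentences in the protocol or analysis plan. It needs no additional recruitment and no change to study conduct. The only cost is a less favourable statement about what the carer comparisons can show.

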### Recruitment of participants

#### GPs

With the exception of Bendigo (which will also include nearby towns as noted above) each site will generate a list of possible GP practices within 30 km of the site headquarters based on lists provided by the local Division of General Practice. Practices will be allocated a random approach order, and will be contacted via phone initially. GPs who express an interest in participation will be visited in order for the study to be explained. Basic demographics will be collected at this visit, from those GPs that agree to participate. It is not expected that all the GPs in a practice will participate. When one or more GPs in a practice consent, the practice as a whole will be allocated to either the intervention or waitlist group. Randomisation will occur at a practice level in order to avoid contamination from patients visiting several GPs who had been randomised to different arms within a single practice.

Randomisation will follow procedures outlined in the CONSORT statement [27]. Practices will be allocated in a ratio of 2:1 to the Intervention or Waitlist group, using an allocation schedule provided independent of the study team, by the Centre for Epidemiology and Biostatistics at the University of Newcastle. The randomisation code has been developed using a computer random number generator to select random permuted blocks. Block lengths of 3 or 6 will be varied randomly. Practices will be stratified by site, and by size of practice as either standard or large (large = more than 7 GPs working in the practice). The intervention group will be kept at twice the size of the waitlist group in order to have sufficient power to compare the effects administering the GPCOG on case finding versus screening patients (see explanation below).

Inclusion criteria for GPs/practices

• Located within 30 kilometres of recruitment centre (with the exception of Bendigo, a rural town)

• Consent to participate in study

• Have patients on a computerised database

• Have patients aged 75 years and over and living in the community

• Consent to being randomised to either intervention waitlist group.

Exclusion criteria for GPs/practices

• Involved in project development

• Does not meet inclusion criteria

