### Case finding and screening

"Case finding" patients will be identified during the patient interview using the following 4 questions:

1. Do you have any complaints about your memory?

2. Have you mentioned these to you GP?

3. If not, have you been intending to tell your GP?

4. Have you sought treatment or taken any remedies such as herbal medications or vitamins specifically for you memory? Please give details.

If questions 2, 3 or 4 are answered in the affirmative, the patient will be considered as a "case finding" patient. Patients identified as having possible or probable dementia on the GP baseline audit will also be considered as a "case finding" patient. All other patients will be identified as "screening" patients - that is, patients who would not receive a cognitive function test unless the GP decided to screen all patients aged over a certain age.

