#### Does case finding or screening produce better results?

Within the Intervention group, the patient outcomes for the group with memory complaints or identified by the GP as having possible or probable dementia (case finding group) will be compared with outcomes for the group without memory complaints or identified memory problems (screening group). Acceptability of the process and satisfaction with care will be particularly examined, both from a quantitative and a qualitative point of view. The performance of the GPCOG in the case finding and screening groups will be compared. In particular positive predictive value, negative predictive value and misclassification rates will be compared. GP audits will be examined to determine how many patients in each group would have a missed diagnosis of dementia if the GPCOG had not been administered.

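### The case finding versus screening comparison in 112 intervention patients with dementia has a two-group power of about 0.66 at the assumed, unsourced 50:50 split, and less if screening patients are the smaller group, not the 0.90 implied

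*Protocol article*

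**What the plan says.** In the protocol article, Sample size starts from the comparison between arms: "45 patients with dementia in each group (Waitlist and Intervention) would give a power of 0.9". The target is 7% for the contrast in change on a WHOQOL-BREF domain, tested at 0.05. The inputs are an SD of 18.5 and a pre-post correlation of 0.7. After an allowance for clustering the requirement is 54 per group. The plan rounds this up to 56 waitlist and 112 intervention patients with dementia, and says the same size also permits the case finding versus screening comparison within the group. The only support offered is: "It is assumed that about 50% of participants will be screening and 50% case finding".

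Recruitment of participants (GPs) rests the allocation ratio on this comparison: "The intervention group will be kept at twice the size of the waitlist group in order to have sufficient power to compare" the two kinds of patient.

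Under Case finding and screening, a patient counts as case finding after having told the GP about memory complaints, having meant to, or having sought treatment or taken remedies for memory. The GP's opinion also counts: "Patients identified as having possible or probable dementia on the GP baseline audit will also be considered as a 'case finding' patient". Everyone else is screening.

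Statistical analyses places the comparison inside one arm: "Within the Intervention group, the patient outcomes for the group with memory complaints or identified by the GP as having possible or probable dementia" are compared with the outcomes of the remaining patients.

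**The concern.** Two things make the power claim doubtful.

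First, the 50:50 split has no stated basis, and the definition pulls against it. Any one criterion is enough to make a patient case finding, and suspicion of dementia on the GP audit bears mainly on patients who have dementia. Among those patients, screening is therefore plausibly the smaller group.

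Second, the step from 112 patients to an adequate comparison treats about 54 per group as enough for 90% power. That is true only if the base figure of 45 per group is right for comparing two groups.

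Aim 2(i) asks which approach gives better outcomes for people with dementia and their carers, and the 2:1 allocation is defended on the ground that this can be answered. If the power is well below 0.90, both statements promise more than the design delivers.

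**Working it through.** **Inputs** (Sample size section unless noted): SD 18.5; correlation 0.7; power 0.90; type 1 error 0.05; ICC 0.05; 5 patients per practice; 112 intervention patients with dementia. Assumptions: two-sided test (sidedness is not stated), and 7% means 7 points on a 0-100 domain score.

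**SD of change:** 18.5 × √(2 × (1 − 0.7)) = 14.33.

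**The plan's base figure.** With 1.960 + 1.282 = 3.242:
- One-sample formula: (14.33 × 3.242 / 7)² = 44.03, rounded up to 45. This matches the plan.
- Two-group formula: 2 × 44.03 = 88.07, that is 89 per group. This does not match.
- The GDS figure behaves the same way. SD of change is 2.39 × √0.6 = 1.851, and the one-sample result is (1.851 × 3.242 / 0.9)² = 44.46, again 45.

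Two groups of 45, before clustering, have power of about 0.64.

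**Design effect.** 1 + (5 − 1) × 0.05 = 1.20, and 45 × 1.20 = 54, the plan's figure. The printed 1.45 would give 65.25, that is 66. I use 1.20.

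**Power of the subgroup comparison**, for groups of size a and b with a + b = 112:

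Φ( 7 / (14.33 × √(1.20 × (1/a + 1/b))) − 1.960 )

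The split among patients with dementia is not in the article, so a range is shown. The last column applies the plan's one-sample formula to the harmonic mean of the two group sizes, divided by 1.20.

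| Case finding : screening | a : b | Harmonic mean | Two-group power | Plan's formula |
|---|---|---|---|---|
| 50:50 | 56 : 56 | 56.0 | 0.66 | 0.92 |
| 60:40 | 67.2 : 44.8 | 53.8 | 0.64 | 0.90 |
| 70:30 | 78.4 : 33.6 | 47.0 | 0.58 | 0.86 |
| 80:20 | 89.6 : 22.4 | 35.8 | 0.47 | 0.76 |

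Worked example at 50:50: √(1.20 × 2/56) = 0.2070; 14.33 × 0.2070 = 2.967; 7 / 2.967 = 2.360; less 1.960 = 0.400; Φ = 0.66.

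**Attribution.** Moving from the one-sample to the two-group formula at 50:50 costs 0.92 − 0.66 = 0.26. On the two-group scale, imbalance then costs a further 0.02 at 60:40, 0.08 at 70:30 and about 0.18 at 80:20.

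**Sensitivity at 50:50.**
- No design effect: 0.73.
- Baseline-adjusted analysis (SD 18.5 × √(1 − 0.49) = 13.21): 0.73 with design effect 1.20. Without a design effect: 7 / (13.21 × √(2/56)) = 2.80; less 1.96 = 0.84; Φ ≈ 0.80.
- Numbers from the Subjects paragraph on drop-outs, taking two thirds as intervention: 120 at 12 months gives 0.69, and 108 at 24 months gives 0.64.

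None of these reaches 0.90.

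**Detectable difference at 90% power, design effect 1.20:** 3.242 × 14.33 × √(1.20 × (1/a + 1/b)) is about 9.6 points for 56:56 and about 10.5 points for 78:34.

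**The case against.** The strongest defence concerns the split. A reader might infer that the 50% was assumed for all 2,000 participants and then misapplied to those with dementia. The text does not support that. The surrounding counts are of patients with dementia, and the next sentence draws from the split a target of 168 participants with dementia. The natural reading is 50% of those with dementia, so nothing is carried over wrongly. What stands is only that the figure has no source.

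A reader might also infer that the screening group will miss 54 and that the claim fails once the split leaves roughly 48:52. The article gives no split from which to predict this, and some of its text limits the shift. The Background says GPs often miss early dementia. A memory complaint alone does not make a patient case finding. Read literally, the audit criterion omits the definite category that the audit form offers. Nor is 54 in the smaller group the right test, because power follows the harmonic mean. On the plan's own formula 0.90 needs a harmonic mean of about 44.03 × 1.20 = 52.8. That holds for a case finding share of about 38% to 62% at 112 patients, 33% to 67% at 120, and 43% to 57% at 108. Moderate imbalance is therefore harmless by the plan's own standard.

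Two further points have weight. The comparison is largely within practices, so a between-practice design effect does not carry over directly; but removing it altogether raises power only to 0.73. And the planned comparison also covers acceptability, satisfaction and the predictive values of the GPCOG, which are not stated to be limited to patients with dementia, so the power statement in the Recruitment section cannot be rejected wholesale.

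**Conclusion.** The concern holds in a limited form. The claim that 112 intervention patients with dementia give adequate power for case finding versus screening on quality of life is not borne out by the plan's inputs. As a two-group comparison of change scores, power is about 0.66 at an even split and falls to 0.58 at 70:30 and 0.47 at 80:20. The main cause is the base of 45 per group; the unsourced split is secondary and matters from about 70:30. That screening will be the smaller group is a plausible inference from the definition, not something the article shows.

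The figures rest on 7% meaning 7 points, a two-sided 0.05 test and a design effect of 1.20. More favourable choices raise power at 112 patients to between 0.73 and about 0.80 at best. The point touches the second aim, not the comparison of randomised arms on the primary outcomes, although the same base figure underlies both.

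**What to change.** Count the case finding and screening patients among intervention patients in the CAMCOG dementia range, from baseline interviews and audits, blind to outcomes. The article reports 2,034 subjects recruited but does not say that all have been classified, so the count may have to wait for the last baseline records.

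In Sample size, replace the bare 50:50 assumption with that split, and restate the power or detectable difference with a two-group formula (about 9.6 points at 90% power for 56:56, about 10.5 for 78:34). In Recruitment of participants, qualify the power statement for the quality of life comparison in patients with dementia; the other purposes of the comparison can stay. If the restated power is below 0.90, report this comparison as an estimate with a confidence interval. The size of the smaller group alone should not decide this.

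The cost is a count and a recalculation, and a less favourable stated power for the second aim. Enrolment and allocation are unaffected.
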